**Pulse wave analysis**

Aortic pressure waveforms will be derived using a generalized validated transfer function (SphygmoCor, AtCor Medical, Sydney, Australia). The aortic pressure wave is composed of a forward wave, caused by stroke volume ejection, and a reflected wave that returns to the aorta from systemic sites. Augmentation pressure is the difference between the second and first systolic peaks. The augmentation index (AIx) will be defined as the augmentation pressure expressed as a percentage of the aortic pulse pressure.

**Blood markers**

A fasting venous blood sample will be collected into evacuated plastic tubes containing ethylenediaminetetraacetic acid (EDTA) before and after the 8-week program. Whole venous blood will be also collected in tubes without anticoagulant for serum preparation. Total cholesterol, triglycerides, high-density lipoprotein cholesterol (HDL-c), low-density lipoprotein cholesterol (LDL-c), fasting glucose, and fasting insulin will be measured. Insulin resistance will be evaluated using the Homeostasis Model of Assessment of Insulin Resistance (HOMA-IR) and will be calculated as [fasting insulin (µU/ml) × fasting glucose (mmol/L)] / 22.5. Circulating irisin levels will be measured using an irisin ELISA kit (Phoenix Pharmaceuticals, CA, USA), and the manufacturer’s instructions will be followed. Serum concentrations of vascular endothelial growth factor (VEGF), endothelial nitric oxide synthase (eNOS), adiponectin, tumor necrosis factor-alpha (TNF-α), high-sensitivity C-reactive protein (hsCRP), and superoxide dismutase (SOD) will be analyzed using ELISA Kits (Cusabio, Biotech. Co., LTD, Wuhan, China), and the manufacturer’s instructions will be followed for each kit.

**Flow cytometric quantification of EPCs**

Quantification of EPCs is defined as CD34^+^/KDR^+^ cells. EDTA-anticoagulated whole blood samples will be labeled with APC-labeled anti-human CD34 (eBioscience) and AlexaFlour488-labeled anti-human KDR (Biolegend) monoclonal antibodies. Fluorescent isotype-matched antibodies will be used as controls. EPCs will be quantitatively measured using a Cytomics FC500 flow cytometer (Beckman Coulter, USA), and acquisition will be stopped after 40,000 events. Data will be analyzed using CXP software 2.0.

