**Primary and secondary outcomes**

Primary outcome is endothelial function which is assessed by FMD. Secondary outcomes include anthropometry, resting heart rate, blood pressure, body composition, aerobic fitness, maximal strength, EPC number and function, arterial stiffness (cfPWV, baPWV, central blood pressure, and augmentation index (AIx)), cardiac autonomic function (standard deviation of normal-to-normal intervals (SDNN), square root of the mean squared differences of successive normal-to-normal intervals (RMSSD), total power (TF), low-frequency power in normalized units (LFnu), high-frequency power in normalized units (HFnu), and low-frequency power/high-frequency power (LF/HF)), and multiple biochemical markers (lipid profiles, insulin, tumor necrosis factor-alpha, high-sensitivity C-reactive protein, superoxide dismutase, vascular endothelial growth factor, endothelial nitric oxide synthase, adiponectin and irisin).

- 1. **Sample size**

Sample size is calculated based on 1% change in FMD after weight loss with an expected standard deviation in FMD from our laboratory of 1.3%. The sample size required for the study, with an α of 0.05 and β of 0.20 at 5% level of significance (two-sided) and estimating a refusal rate of 20%, is 20 subjects.

- 1. **Measurement procedures**

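### Flow cytometry stops at 40,000 events with no stated parent population and no minimum CD34+/KDR+ count, so the precision of EPC number is not secured

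*Protocol*

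**What the plan says.** The section on flow cytometric quantification of EPCs sets the target population: "Quantification of EPCs is defined as CD34^+^/KDR^+^ cells". The specimen is antibody-labelled EDTA whole blood, and "acquisition will be stopped after 40,000 events". The section does not say whether these are all events or events inside a cytometry gate such as mononuclear cells. It gives no minimum number of double-positive cells, no expected frequency, and no unit for the result (share of events or cells per volume). Mononuclear cells are isolated only under EPC culture, for the functional assays.

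The Objective section names the number of EPCs, and the outcomes section lists "EPC number and function" among the secondary outcomes. The primary outcome is separate: "Primary outcome is endothelial function which is assessed by FMD". Sample size rests on FMD alone. The Data analysis section plans paired t-tests for before-after change and Pearson correlations for associations.

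**The concern.** When a rare population is counted, relative precision depends on how many target cells are seen, not on how many events pass the detector. A fixed stop on events, with no floor on target cells, lets the target count fall wherever the frequency puts it.

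In a paired before-after comparison this error enters twice, once per visit, while stable differences between subjects cancel. If the count is small, counting error can take up a large part of the variation in EPC change. A real change could then be missed, correlations that use EPC number would be weakened, and a null result would be hard to interpret. Events not acquired cannot be recovered once the sample is gone.

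**Working it through.** **Number of pairs.** The protocol has no EPC precision figure to reproduce. Its one related figure is the sample size of 20: "Sample size is calculated based on 1% change in FMD after weight loss", with an "expected standard deviation in FMD from our laboratory of 1.3"%. Reading 1.3 as the SD of change, a paired t-test at two-sided 5% with 80% power needs n = 16 (power 0.820), and 16/(1 − 0.20) = 20. The stated figure is reproduced. The EPC analysis therefore has about 16 pairs.

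**Inputs.** From the protocol: 40,000 events per sample, 16 pairs, paired analysis. Assumed: the share f of acquired events that are CD34+/KDR+, taken as 0.01% to 0.1%; the same expected count at both visits; Poisson counting; and an SD of true within-subject change of 30% of baseline.

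**Formulas.** Expected count m = 40,000 × f. Counting CV per sample = 1/√m. Counting CV of one subject's post/pre ratio ≈ √(2/m), a first-order approximation that is rough at m = 4. Counting error of the mean change = √(2/m)/√16. Counting share of the paired-difference variance = (2/m)/(2/m + 0.30²). Attenuation of a correlation with EPC-number change = √(1 − share).

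| Assumed f | 0.01% | 0.02% | 0.05% | 0.1% |
|---|---|---|---|---|
| Target cells, m | 4 | 8 | 20 | 40 |
| CV per sample | 50% | 35% | 22% | 16% |
| CV of post/pre ratio | 71% | 50% | 32% | 22% |
| Error of mean change, 16 pairs | 18% | 12.5% | 8% | 6% |
| Share of paired-difference variance | 85% | 74% | 53% | 36% |
| Attenuation factor | 0.39 | 0.51 | 0.69 | 0.80 |

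Example at 0.01%: 2/4 = 0.50, and 0.50/(0.50 + 0.09) = 0.85.

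**Detectable change.** From counting error alone, the mean change detectable with 80% power is (1.96 + 0.84) times the error of the mean: about 50/35/22/16% of baseline (normal approximation). Biological variation would add to this.

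**Sensitivity to the assumed change SD.** Counting error exceeds half the paired-difference variance when 2/m is larger than the squared SD. For an SD of 50%, 30% or 20% this means m below 8, 22 or 50, that is, f below about 0.02%, 0.056% or 0.125%.

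**Effect of a larger acquisition.** At 500,000 events the counting CV falls by √(500,000/40,000) = 3.5, giving 50/100/250/500 cells and CVs of 14/10/6.3/4.5%. A count of 100 cells (CV 10%) needs 1,000,000/500,000/200,000/100,000 events across the same range. With 100 cells per visit the counting share is 0.02/(0.02 + 0.09) = 18%, and the error of the mean change is √0.02/4 = 3.5%.

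**The case against.** A reader might infer that the stop leaves only a handful of target cells, or that EPC number is mostly counting noise. The documents support neither as a fact. They give no CD34+/KDR+ frequency, no variability of EPC number and no parent population for the 40,000 events. At 0.05% to 0.1% the count is 20 to 40. If the events are counted inside a mononuclear gate, the frequency among them is higher than among all events, and the counts rise. That stands.

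The share of variance also depends on the comparator. Against an assumed between-subject CV of 50% at a single visit, counting error is only 50/33/17/9% of the variance. That comparison is fair for single-visit correlations. It is not the right one for the planned paired t-test, where stable differences between subjects cancel and counting error does not.

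Three further limits stand. The per-subject ratio CV is four times the counting error of the group mean with 16 pairs. Counting error widens the interval but does not bias the mean change. And the effect reaches only analyses that use EPC number: migration and adhesion are measured on cultured cells and do not depend on this stop, nor do FMD and the sample size. The protocol does not name EPC number among its planned correlations, so attenuation applies only if such correlations are run. It also states no expected EPC change, so one cannot say that noise would swamp a realistic effect.

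**Conclusion.** The point holds in conditional form. The protocol fixes a stopping rule that does not secure the precision of EPC number, because neither the parent population nor a minimum target count is stated. Over the assumed range of 0.01% to 0.1%, the counting error of the mean change runs from about 18% down to 6% of baseline. Counting takes about 85% down to 36% of the paired-difference variance if true change has an SD of 30%. Whether counting error dominates turns on three quantities that the documents do not give: frequency, parent population and biological variability of change. The matter concerns precision in one secondary outcome. It does not threaten the primary outcome, but it is worth correcting because the rule is explicit, the outcome is named in the objective, and the remedy is cheap.

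**What to change.** In the flow cytometry section:

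- State the cytometry gate to which the event count applies, and how EPC number is expressed.
- Replace the 40,000-event stop with a minimum number of CD34+/KDR+ events, for example 100 where the sample allows, or with a much larger total. The two are not equivalent: 500,000 events would give only about 50 target cells at 0.01%, where 100 cells needs about 1,000,000. A minimum target count fixes the precision directly.
- Apply the same rule before and after the program, and record the number of positive events with each result so that the precision achieved can be seen.

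The cost is longer acquisition per tube and possibly slightly more of the blood already drawn. The protocol gives no volume for the cytometry sample, so check that it suffices. No new procedure is needed.

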**EPC culture**

For EPC culture, 10 ml of peripheral blood will be obtained from obese subjects, and total mononuclear cells will be isolated by density gradient centrifugation (400 g for 30 min) with Histopaque-1077 (Sigma, St. Louis, MO, USA). Then mononuclear cells will be cultured on fibronectin-coated 6-well plates in M199 medium supplemented with 20% FBS, 100 U/ml penicillin, 100 µg/ml streptomycin, and 10 ng/ml VEGF. After 4 days in culture, nonadherent cells will be removed. Adherent cells will be maintained until day 7 and then used for EPC functional assays.

**EPC migration assay**

For EPC migration assay, a total of 2×10^4^ isolated EPCs will be resuspended in 250 µl serum-free M199 medium and placed in the upper chamber of a modified Boyden chamber (Costar Transwell assay, 8 µm pore size; Corning, NY, USA). The chamber will be placed in a 24-well culture dish containing 500 µl M199 medium supplemented with 10 ng/ml VEGF. After a 24-hour incubation at 37˚C, the membrane will be washed briefly with phosphate-buffered saline (PBS) and fixed with 4% paraformaldehyde. The membrane will be then stained using 0.1% crystal violet solution and carefully removed. The transmigrated cells will be counted manually in three random microscopic fields (×200) by independent, blinded investigators.

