**EPC adhesion assay**

For the EPC adhesion assay, EPCs will be isolated and resuspended in M199 medium with 5% FBS. An equivalent amount of cells will be placed on a fibronectin-coated 96-well plate and incubated at 37˚C in 5% CO_2_ for 6 hours. After two gentle washes with PBS, adherent cells will be counted by independent, blinded investigators.

- 1. **Data analysis**

Analyses will be performed using SPSS 16.0 (SPSS 16, SPSS Inc., Chicago, IL, USA). Paired-sample t-tests will be used to compare the effects of an 8-week intervention of exercise and diet on different variables. Pearson’s correlation will be calculated to determine associations. The descriptive analyses will calculate the mean and standard deviations for continuous and percentages for categorical variables. A P-value < 0.05 will be used to indicate statistical significance.

•

•

•

•

1. **References**

Brook, R.D. (2006). Obesity, weight loss, and vascular function. *Endocrine* 29(1)**,** 21-25. doi: 10.1385/ENDO:29:1:121.

Collaboration, N.C.D.R.F. (2016). Trends in adult body-mass index in 200 countries from 1975 to 2014: a pooled analysis of 1698 population-based measurement studies with 19.2 million participants. *Lancet* 387(10026)**,** 1377-1396. doi: 10.1016/S0140-6736(16)30054-X.

Korkmaz, H., and Onalan, O. (2008). Evaluation of endothelial dysfunction: flow-mediated dilation. *Endothelium* 15(4)**,** 157-163. doi: 10.1080/10623320802228872.

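### EPC migration is read from only three random fields per membrane, which adds avoidable sampling error to a secondary outcome; the power lost depends on variances the protocol does not give

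*Protocol*

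**What the plan says.** The EPC migration assay section of the protocol describes one chamber per sample, loaded with "a total of 2×10^4^ isolated EPCs". After incubation the membrane is "fixed with 4% paraformaldehyde", then stained and removed. The reading rule is: "The transmigrated cells will be counted manually in three random microscopic fields (×200) by independent, blinded investigators". The section gives no replicate chambers, field positions, area counted or minimum cell count. It does not say whether all investigators read the same fields.

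The outcomes section lists "EPC number and function" among the secondary outcomes, and the objective also names EPC function. Under Data analysis, "Paired-sample t-tests will be used to compare the effects of an 8-week intervention", and Pearson correlations are planned for associations. The sample size rests on FMD alone: "1% change in FMD after weight loss with an expected standard deviation in FMD from our laboratory of 1.3"%, 80% power at a two-sided 5% level and, "estimating a refusal rate of 20%, is 20 subjects".

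**The concern.** A count from three fields is a small sample of a membrane. Even if cells settle entirely at random, counts vary from field to field by chance, and any clustering adds to that. The mean of three fields therefore misses the membrane's true mean by an amount unrelated to the subject. This happens before and after the programme, so the paired difference takes the error twice.

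Random field choice and blinding protect against bias but do not reduce this variance. With about 16 to 20 pairs there is little room to absorb it. Added noise in the migration change lowers the power of its t-test and pulls its correlations with other changes, such as FMD, towards zero. The noise is avoidable because the fixed, stained membrane can be read further without more blood, cells or culture.

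**Working it through.** **The plan's own figure.** The only sample size is for FMD. With a change of 1, an SD of 1.3, two-sided 0.05 and a paired t-test (noncentral t), power is 79% at n = 15 and 82% at n = 16. Allowing for 20% refusal, 16 / 0.8 = 20, so the stated 20 reproduces. I use n = 16 below. No effect, SD or power is stated for migration.

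**Model.** Let k be the number of fields, c the field-to-field CV within a membrane, and s the between-person SD of the true change (both as % of the mean).

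- Reading error per visit: c / √k
- Reading error on the paired change: c × √(2/k)
- SD of the observed change: √(s² + 2c²/k)
- Power: paired t-test with standardised effect 25 / √(s² + 2c²/k), n = 16, two-sided 0.05

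The 25% gain, c and s are all assumptions; the protocol supplies none of them. Only k = 3 and the paired t-test come from the text. Going from 3 to 10 fields cuts the reading variance by 1 − 3/10 = 70%, whatever c is.

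**Worked case.** With c = 30 and s = 25:
- k = 3: reading SD 30 × √(2/3) = 24.5; total √(625 + 600) = 35.0; power 76%.
- k = 10: reading SD 30 × √(2/10) = 13.4; total √(625 + 180) = 28.4; power 91%.
- A correlation of the migration change with an error-free variable is multiplied by 25/35.0 = 0.71 with 3 fields and 25/28.4 = 0.88 with 10.

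**Power, 3 fields against 10 fields, n = 16, 25% true gain:**

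| Field CV | SD of change 25% | SD 35% | SD 50% |
|---|---|---|---|
| 10% | 94% vs 96% | 74% vs 76% | 46% vs 46% |
| 20% | 88% vs 94% | 68% vs 74% | 43% vs 45% |
| 30% | 76% vs 91% | 59% vs 70% | 39% vs 44% |
| 50% | 50% vs 80% | 41% vs 62% | 31% vs 40% |

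**Which field CVs are possible?** Random (Poisson) scatter alone gives a field CV of 1/√m at a mean of m cells per field, so m must be at least 1/CV²: 100 cells for a CV of 10%, 25 for 20%, about 11 for 30% and 4 for 50%. Poisson scatter alone puts √(2/(3m)) on the three-field change: 37%, 26%, 18% and 12% at m = 5, 10, 20 and 50. The protocol gives no expected count, so it does not settle which row applies.

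**Variation that more fields cannot reduce.** If chamber and culture add a CV of 20% per visit (again an assumption), the worked case becomes √(625 + 800 + 600) = 45.0 with 3 fields and √(625 + 800 + 180) = 40.1 with 10. Power is 55% against 65%, a gain of 10 points instead of 15.

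**The case against.** The case for leaving the rule alone has substance.

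- **The text contains no error.** The rule is clear, the fields are random and the readers are blinded. More fields always give more precision, which does not by itself make three inadequate. That is why this is an improvement and not a correction.
- **Every number that drives the size is assumed.** A reader might infer that field variation matches the biological variation and costs the outcome much of its power. The documents do not support that: it needs, for example, a field CV of 30% together with an SD of change of 25%. At field CVs of 10–20% the gain from 10 fields is about 1 to 6 points, and at an SD of 50% it never exceeds about 10.
- **Three may understate the sampling.** The protocol speaks of investigators in the plural and does not say that they share fields. If two readers each choose three, six fields are read, and power in the worked case is already 87%, against 91% with ten. If they share the same three, extra readers do nothing for field sampling error.
- **Sixteen may be pessimistic.** The 20% is called a refusal rate, and subjects live in a closed, supervised camp. With all 20 evaluable, three fields give 86% in the worked case.
- **Other variation may dominate.** Seven-day culture and a single chamber may contribute more than the fields do.

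These points limit the size. None of them reverses the direction or makes the extra reading costly.

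**Conclusion.** The point holds as a cheap improvement to a secondary outcome. Reading three fields adds sampling error that enters the paired change twice, and ten fields remove about 70% of that variance. The gain in power runs from under 1 point to about 30, given a 25% true gain, 16 evaluable subjects, field CVs of 10–50%, SDs of change of 25–50%, three fields in total and no chamber or culture variation in the model. Relaxing either of the last two conditions shrinks it.

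It does not follow that the migration analysis is underpowered as planned. The protocol claims no power for it and gives nothing from which to calculate one. The FMD outcome and its sample size are unaffected.

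**What to change.** In the EPC migration assay section, replace the three random fields with at least 10 fields per membrane at preset positions covering centre and edge. Use the same grid at both visits and the same fields for all readers, and define the outcome as the mean over fields and readers. Ten is a practical number and is not derived from the protocol. Preset positions also remove reader discretion, since no procedure for choosing random fields is given.

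The cost is a few more minutes of reading per membrane by the same blinded investigators. No extra blood, cells, culture or staff are needed.

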**EPC adhesion assay**

For the EPC adhesion assay, EPCs will be isolated and resuspended in M199 medium with 5% FBS. An equivalent amount of cells will be placed on a fibronectin-coated 96-well plate and incubated at 37˚C in 5% CO_2_ for 6 hours. After two gentle washes with PBS, adherent cells will be counted by independent, blinded investigators.

- 1. **Data analysis**

Analyses will be performed using SPSS 16.0 (SPSS 16, SPSS Inc., Chicago, IL, USA). Paired-sample t-tests will be used to compare the effects of an 8-week intervention of exercise and diet on different variables. Pearson’s correlation will be calculated to determine associations. The descriptive analyses will calculate the mean and standard deviations for continuous and percentages for categorical variables. A P-value < 0.05 will be used to indicate statistical significance.

•

•

•

•

1. **References**

Brook, R.D. (2006). Obesity, weight loss, and vascular function. *Endocrine* 29(1)**,** 21-25. doi: 10.1385/ENDO:29:1:121.

Collaboration, N.C.D.R.F. (2016). Trends in adult body-mass index in 200 countries from 1975 to 2014: a pooled analysis of 1698 population-based measurement studies with 19.2 million participants. *Lancet* 387(10026)**,** 1377-1396. doi: 10.1016/S0140-6736(16)30054-X.

Korkmaz, H., and Onalan, O. (2008). Evaluation of endothelial dysfunction: flow-mediated dilation. *Endothelium* 15(4)**,** 157-163. doi: 10.1080/10623320802228872.

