**Heart rate variability**

HRV is used to determine the autonomic activity. The subjects will rest in the supine position for at least 10 min before the data are collected using the SphygmoCor device (AtCor Medical, Sydney, Australia). As for the time domain analysis, we will determine the standard deviation (SD) of normal-to-normal (NN) intervals (SDNN) and square root of the mean squared differences of successive NN intervals (RMSSD). SDNN is a measure of overall HRV, so a lower SDNN level indicates reduced overall HRV. RMSSD is a measure of parasympathetic autonomic function, and a reduced RMSSD is a marker of parasympathetic loss. For frequency domain analysis, total power (TP) in the frequency (0-0.40 Hz) will be divided into low-frequency power (LF: 0.04-0.15 Hz, modulated mainly by sympathetic system) and high-frequency power (HF: 0.15-0.40 Hz, modulated by parasympathetic system). Normalized units (nu) will be calculated by dividing the power of LF or HF by (LF+HF). LF/HF ratio reflects the complex interplay between sympathetic and parasympathetic modulation (sympathovagal balance). Increased sympathovagal balance is considered to reflect predominant sympathetic activity.

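### One unadjusted P < 0.05 rule covers FMD, some 33 to 37 secondary variables and an unspecified set of correlations, none labelled exploratory, and two of those variables (LFnu and HFnu) are the same test

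*Protocol*

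**What the plan says.** Under Primary and secondary outcomes, the protocol states: "Primary outcome is endothelial function which is assessed by FMD". The sample size of 20 is derived from FMD alone. The same section then gives a long list that begins "Secondary outcomes include anthropometry, resting heart rate, blood pressure, body composition, aerobic fitness, maximal strength, EPC number and function, arterial stiffness" and goes on to six heart rate variability indices and a panel of blood markers. It does not say how many secondary variables there are.

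The Data analysis section plans paired t-tests for the before-after comparison of the variables. It adds that Pearson's "correlation will be calculated to determine associations", without naming the pairs or saying whether baseline, post-programme or change values are used. It closes with "A P-value < 0.05 will be used to indicate statistical significance". No adjustment, hierarchy or exploratory label is attached to anything.

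The Objective covers endothelial function, EPC number and function, autonomic function, arterial stiffness and the mechanisms behind the effects. The Heart rate variability section defines the normalised indices: "Normalized units (nu) will be calculated by dividing the power of LF or HF by (LF+HF". LFnu, HFnu and LF/HF are listed as separate secondary outcomes.

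**The concern.** The protocol sets up a hierarchy when it names FMD as primary and sizes the study on it, and then states a decision rule that ignores it. Under that rule, a P of 0.04 for irisin, for baPWV or for any correlation is declared significant in the same terms as a P of 0.04 for FMD.

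Two things are at stake. First, chance changes among the secondary outcomes can be reported as effects of the programme, and chance correlations as mechanisms. The mechanism claims are the more exposed, because correlation is the only planned analysis that relates one variable to another and its scope is open. Second, variables that are algebraically tied can be counted as separate findings that appear to support each other.

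**Working it through.** **1. The plan's own sample size.** Inputs, from the Sample size section: a "1% change in FMD after weight loss with an expected standard deviation in FMD from our laboratory of 1.3" per cent, two-sided alpha 0.05, power 80%, 20% refusal.
- Paired t-test by the noncentral t distribution, taking 1.3 as the SD of the paired change: n = 16, power 82.0%.
- 16 / (1 − 0.20) = 20, which matches the protocol.
- The normal approximation gives (1.3 × (1.960 + 0.842) / 1)² = 13.3, so 14, and 14 / 0.8 = 17.5, so 18.

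The study is therefore sized for one test, on FMD. About 16 evaluable people is a derived figure (20 × 0.8). It treats refusal as loss after enrolment.

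**2. Number of secondary variables.** From the secondary outcome list:

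| Group | Variables | Count |
|---|---|---|
| Anthropometry and body composition | weight, BMI, one body-composition measure | 3 |
| Haemodynamics | resting HR, SBP, DBP | 3 |
| Fitness | PWC, 1RM | 2 |
| EPC | number, migration, adhesion | 3 |
| Arterial stiffness | cfPWV, baPWV, one central pressure, AIx | 4 |
| Autonomic | SDNN, RMSSD, total power, LFnu, HFnu, LF/HF | 6 |
| Lipids and insulin | total, HDL and LDL cholesterol, triglycerides, insulin | 5 |
| Other markers | TNF-α, hsCRP, SOD, VEGF, eNOS, adiponectin, irisin | 7 |
| **Total** | | **33** |

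The measurement sections add second-device cfPWV, fasting glucose, HOMA-IR and nitroglycerine-mediated dilation: 33 + 4 = 37.

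**3. Chance of at least one false significant secondary result.** For k independent null tests this is 1 − 0.95^k, and the expected number of false positives is 0.05k.

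| Assumption | Chance of at least one |
|---|---|
| 33 null, independent | 81.6% |
| 37 null, independent | 85.0% (1.85 expected) |
| 37 null, common correlation 0.3 | 74% |
| 37 null, common correlation 0.5 | 58% |
| 37 null, common correlation 0.7 | 40% |
| only 20 null, independent | 64% |
| only 10 null, independent | 40% |
| only 5 null, independent | 23% |

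The correlated rows come from simulation (n = 16, 5,000 runs each). The protocol gives neither the correlations nor the number of true nulls, so these are assumptions shown as a range.

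**4. Correlations.** No error rate follows from the protocol, because the number of pairs is not given. If the tested pairs included 5, 10 or 20 independent nulls, the formula in step 3 would again give 23%, 40% or 64%. On precision: at n = 16, P < 0.05 requires |r| > 0.497, and an observed r of 0.5 has a 95% interval of about 0.01 to 0.80.

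**5. The heart rate variability indices.** By definition LFnu = LF/(LF+HF) and HFnu = HF/(LF+HF), so LFnu + HFnu = 1 for each person at each visit.
- Change in HFnu = (1 − LFnu after) − (1 − LFnu before) = −(change in LFnu).
- The mean change reverses sign and its SD is unchanged, so t reverses sign, and |t| and P are identical.
- LF/HF = LFnu/(1 − LFnu). This is a nonlinear function of the same quantity. Its paired t-test can give a different P, but it carries no new information.

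**The case against.** The strongest objection is that only the protocol is at hand, and that adjustment among secondary outcomes and the list of correlation pairs are ordinary SAP content. Had the protocol been silent, that would settle the matter. It is not silent: it fixes one significance rule for all tests, and an SAP that downgraded or adjusted the secondary tests would have to depart from that rule.

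It can also be said that naming a single primary outcome already protects the main conclusion. That stands: FMD is tested once at 5%.

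Several stronger readings are tempting, and the document does not support them.
- A reader might infer that a false positive among the secondary outcomes is close to certain. The 85% figure needs all 37 to be null and independent. Weight, BMI and fitness are unlikely to be null under this training and diet, and many variables are tied together (the HRV indices, the two cfPWV measurements, insulin, glucose and HOMA-IR).
- A reader might take the correlations to be an all-by-all screen. Among 38 variables that would be 38 × 37 / 2 = 703 pairs, with about 35 false positives if all were null. The protocol leaves the set unspecified. It does not say that every pair will be tested, nor that before and after values will be pooled.
- A reader might blame the small sample. Sample size does not raise the type I error of a valid test. It makes the estimates imprecise, which is a separate matter.

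Finally, an exact duplicate such as HFnu adds nothing to the family-wise error rate. That is right. The harm is in reporting, where one change appears as two or three findings.

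**Conclusion.** The point holds as a weakness in the stated decision rule. It is not a threat to the primary result. One unadjusted threshold governs FMD, about 33 to 37 secondary variables and an unspecified set of correlations, with nothing marked exploratory. Under the scenarios examined, the chance of at least one false significant secondary result lies between about 23% and 85%, well above 5%. The upper figure is a ceiling that requires all 37 to be null and independent. The lower one assumes only 5 independent nulls, and would be lower still if those few were also correlated.

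The LFnu/HFnu duplication needs none of these assumptions, since it follows from the protocol's own formula. The change should be made: the primary conclusion survives without it, but the EPC, stiffness, autonomic and mechanism claims are exposed.

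**What to change.** Replace the closing sentence of the Data analysis section with wording such as:

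> The paired test of the change in FMD (two-sided, 0.05) is the only confirmatory test. All secondary outcomes and correlations are exploratory and are reported with 95% confidence intervals. Correlations are limited to a short list of change-versus-change pairs named before the data are analysed, are FDR-adjusted, and are described as hypothesis-generating.

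Test only one of LFnu and HFnu, or ln(LF/HF) in their place, and report the others descriptively.

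Full adjustment of the secondary outcomes is a debatable trade-off and is not needed for this fix. A Bonferroni threshold of 0.05/37 = 0.00135 would cut power for a standardised change of 1/1.3 = 0.77 at n = 16 from 82% to about 26%.

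The cost is that fewer secondary results can be called significant, the correlation list must be written in advance, and the remaining LFnu, HFnu and LF/HF indices become descriptive. No new participants or measurements are needed, and the FMD test loses no power.
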